
**Figure 1 f1:**
[figure not shown]
Overview of the study protocol. EUS-FNB, endoscopic ultrasound with fine needle biopsy.

### Graphic novel or comic panel

The authors created a comic panel consisting of a sequence of six colorful vignettes in which the routine procedure of an EUS-FNB is described to the patient (**Figure 2**). The authors focused on various graphical aspects of comics, such as the facial expressions of the characters and the background, both made to look similar to the effective contexts experienced by patients at the institute. The initial drafts of the six vignettes were created using artificial intelligence (AI image creator using DALL-E3 technology) and later modified by one author ([name]) using graphical software (GIMP, GNU Image Manipulation Program, version 2.10.28, gimp.org).

**Figure 2 f2:**
[figure not shown]
The graphic novel created to administer to patients randomized to the test group.

### Assessing anxiety

After EUS-FNB, all the recruited patients will receive the Beck Anxiety Inventory (BAI) (16) and a modified version of the Depression Anxiety Stress Scales-21 (mDASS-21) (17) (**Figure 1**). Prior to the endoscopic procedures (i.e., EUS-FNB), these questionnaires will be administered anonymously in a mixed paper-pencil and/or QR code mode to be used with a personal mobile phone. A physician, nurse or clinical assistant will be present for questions and clarification. The BAI is a 21-question self-report inventory used to assess anxiety severity in adults older than 17 years. Respondents answer questions about common anxiety symptoms, such as numbness, tingling, sweating unrelated to heat, and fear of catastrophic events. The BAI takes approximately 5 to 10 min to complete. Scores range from 0 (not at all) to 3 (severe), with higher scores indicating more severe anxiety. Standardized cutoffs classify anxiety levels as minimal, mild, moderate, or severe. The other questionnaire is a modified version of the DASS-21, which originally consisted of 21 items divided into three subscales (anxiety, stress, and depression) with seven items each. We focused on the anxiety and stress subscales, so we modified the questionnaire by removing the depression subscale. Specifically, the anxiety subscale assesses physiological arousal, situational anxiety, and subjective experience of the effects of anxiety, while the stress subscale evaluates chronic non-specific arousal, difficulty in relaxing, nervous tension, irritability, agitation, impatience, and overactivity. Each item is rated on a 4-point scale from 0 (did not apply to me at all) to 3 (applied to me very much, or most of the time). The total score for each subscale ranges from 0 to 14 in our modified version, with higher scores indicating higher levels of anxiety and stress. We named this modified version mDASS-21 or mASS-14. The mASS-14 has four cutoff points to classify anxiety and stress levels: normal (0–4), mild (5–8), moderate (9–11), or severe (12–14). Since the DASS-21 is a reliable and valid measure of anxiety and stress symptoms with good internal consistency, test–retest reliability, and discriminant validity, we will evaluate its modified version in our scenario. Both the BAI (**Figure 3**) and mDASS-21 (**Figure 4**) used in this pilot study were in the Italian versions to avoid language barriers.

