## Abstract

The utilization of graphic novels in the realm of clinical medicine is an infrequent occurrence. However, there is a burgeoning interest in their application across a spectrum of pathological conditions with the ultimate aim of enhancing patient care. This study is a prospective pilot designed to assess the influence of graphic novels on the stress levels and behavioral responses of patients diagnosed with pancreatic lesions and who are to undergo endoscopic ultrasound-guided fine needle biopsy (EUS-FNB). Patients exhibiting radiological and clinical pancreatic lesions needing biopsy will be evaluated consecutively. The inclusion criteria encompass the presence of a solid pancreatic mass or a partially solid mass in the event of a cystic component. The exclusion criteria include patients with cognitive impairments, those currently on benzodiazepines or other psychotropic medications, and those with a prior diagnosis of cancer. The authors have developed a comic panel comprising a sequence of six vibrant vignettes, which delineate the standard procedure of EUS-FNB to the patient. Following hospital admission, patients who meet the enrolment criteria and consent to participate in the study will be randomly assigned to either the test or the control group. A graphic novel will be distributed to all patients in the test group, who will have the opportunity to peruse it while awaiting the procedure. Subsequent to the EUS-FNB, all enrolled patients will complete the Beck Anxiety Inventory (BAI) and a modified version of the Depression Anxiety Stress Scales-21 (termed mDASS-21 or mASS-14). The BAI, a 21-item self-report inventory, is employed to gauge the severity of anxiety in adults. The other questionnaire is a modified rendition of the DASS-21, which originally comprised 21 items segregated into three subscales (anxiety, stress, and depression) with seven items each. The anxiety subscale measures physiological arousal, situational anxiety, and the subjective experience of the effects of anxiety, while the stress subscale assesses chronic non-specific arousal, difficulty relaxing, nervous tension, irritability, agitation, and impatience.

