## Introduction

Endoscopy, specifically endoscopic ultrasound (EUS), alongside laparoscopic surgery, is the principal modality for the diagnosis and treatment of severe and occasionally life-threatening pancreatic disorders. Particularly in the context of pancreatic lesions, diagnostic procedures such as EUS with fine needle biopsy (EUS-FNB) can induce states of fear and anxiety in patients. The apprehension and/or anxiety associated with the biopsy procedure may be disproportionate relative to the actual risks or objective threat (1). Waiting for a biopsy can be fraught with fear (“What if it is cancer?”), given that a cancer diagnosis is arguably one of the most stressful, life-altering events an individual can encounter (2). The term graphic medicine was coined by a consortium of researchers, clinicians, and artists to describe a new subfield of research and practice (3). It can be defined as a form of visual storytelling exploring narratives in healthcare, cancer, healing, and disability (4). Graphic medicine is currently a trending topic in health communication, with messages contained within the storytelling of health communication being increasingly described as “creative” and “compelling” (5). Researchers are also demonstrating growing interest in graphic narratives, which continue to emerge as efficacious communication tools in public health (6, 7). Various authors theorize the role of storytelling with comics in shaping behaviors, as in the case of anxiety reduction. Graphic medicine is considered effective by many practitioners because it provides medical professionals with an innovative approach to information dissemination, which is both rapid and comprehensive (8). Graphic medicine uses sequential (though not always narratively linear) visual storytelling to convey health-related experiences or information (9). The use of comics facilitates soft skills, thereby opening up a space in which care professionals can communicate effectively with patients while they are going through emotionally charged situations. With their combination of images, limited text, and relatively short format, comics provide an easy option for the effective communication of health-related messages (10). Consequently, graphic novels have been applied to several fields, including oncology (11), HIV infection (12), eating disorders (13), and oral cancer (14). To date, there have been no applications in the field of endoscopy, so the aim of the present study is to evaluate, for the first time in the literature, the efficacy of colorful graphic novels in reducing anxiety in adult patients waiting for an endoscopic-guided biopsy for pancreatic lesions.

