
## Materials and methods

### Study design

This is a prospective pilot study evaluating the influence of graphic novels on the stress levels and behavioral responses of patients diagnosed with pancreatic lesions and who are to undergo EUS-FNB. The study is being conducted at ISMETT (Istituto Mediterraneo per i Trapianti e Terapie ad Alta Specializzazione), IRCCS (Istituto di Ricovero e Cura a Carattere Scientifico) or the Scientific Institute of Hospitalization and Care in collaboration with UPMC Italy (University of Pittsburgh Medical Center, Italy), located in Palermo, Italy. The study adheres to the principles of the Declaration of Helsinki regarding experimentation involving human subjects, and written informed consent will be procured from all enrolled participants. The protocol is under evaluation of the ethical committee with number IRRB/43/23 and it is registered to ClinicalTrials.gov (NCT06268106). The authors will consecutively evaluate all patients with radiological and clinical suspicion of a pancreatic lesion from from May 2024 to October 2024. The inclusion criteria are (1) age ≥ 18 years; (2) pancreatic solid mass or partially solid in the case of a cystic component requiring tissue acquisition; (3) agreement to participate in the study by signing the informed consent form, and the ability to read and understand the informed consent form; and (4) patients not affected by any known psychological disorder. The exclusion criteria are (1) patients with cognitive deficits, such that they cannot adequately complete the questionnaire, and the visually impaired; (2) suspected or obvious pregnancy status in female patients; (3) patients using benzodiazepines or other psychotropic medications; and (4) patients with a previous diagnosis of cancer. Following hospital admission, patients successfully enrolled and consenting to participate in the study will be randomly allocated to the test or control group using dedicated software (Random Allocation Software, version 1.0) (15). Patients randomized to the control group will experience the standard daily routine in case of EUS-FNB of a pancreatic lesion at our institute, including procedure explanation and consent acquisition. Moreover, it will include an initial colloquium with physical examination, during which the physician explains how the day will unfold, addressing any procedure-related and medical care-related questions the patient may have. After the initial explanation of the daily medical routine, the physician will ask the patient to read the informed consent and to sign it, if they agree. The patient then waits in their room until it is their turn to be brought to the endoscopic room for the EUS-FNB. In case of randomization to the test group (**Figure 1**), the graphic novel will be provided to the patients after the initial colloquium, leaving them waiting for the procedure with the graphic novel, allowing them to read it while waiting and to assimilate slower how their day will unfold.

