## Discussion

The utilization of graphic narratives in the medical field, though not widespread, is gaining recognition for its potential in patient care management across various pathological conditions. The American Cancer Society has pioneered this approach in cancer prevention, employing a comic book to address the barriers to cervical cancer screening. This innovative method bridges contemporary research with historical public health communication efforts, highlighting the promising attributes of this tool (11). In the sensitive domain of acquired immunodeficiency syndrome (AIDS), comic books have contributed positively to the discourse surrounding this infectious and severe condition (12). Therefore, graphic narratives have been demonstrated to encourage true education, understanding, and empathy. Another significant role of graphic novels is their impact on stress and anxiety management in patients awaiting biopsy for potentially malignant disorders. In a recent open-label randomized clinical trial, graphic novels significantly improved the ability of patients to tolerate anxiety while waiting for an oral biopsy in suspected oral cancers (14). Nowadays, feelings of anxiety and stress are pervasive, which can increase in the case of doubtful health conditions needing medical procedures, such as a pancreatic lesion biopsy. Patients can experience intense and immediate fear and/or anxiety prior to an endoscopic treatment and/or pancreatic biopsy, and this discomfort typically manifests in the waiting room, possibly leading to negative intrusive thoughts (e.g., “It will hurt.” or “I will be diagnosed with a terrible disease.”) (18). Graphic novels are emerging as valuable medical tools to support patient care, and comics can easily communicate concepts by telling stories with relevant characters, settings, and situations. Our pilot study aims to give novel data about the impact of this tool in clinical practice for improving clinical psychological patient conditions associated with diagnostic procedures. In the near future, the results of this pilot study could guide physicians and companies in designing new clinical trials to evaluate graphic novels in clinical practice in the management of anxiety and stress tolerance.

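### The protocol article places the BAI and mDASS-21 both after and before EUS-FNB; scores taken afterwards may not capture the waiting anxiety that the trial aims to reduce

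*Protocol article*

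**What the plan says.** Three statements in the protocol article fix when the BAI and mDASS-21 are completed.

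- Assessing anxiety, first sentence: "After EUS-FNB, all the recruited patients will receive the Beck Anxiety Inventory (BAI", with the mDASS-21 named alongside it and Figure 1 cited.
- Assessing anxiety, second sentence: "Prior to the endoscopic procedures (i.e., EUS-FNB), these questionnaires will be administered anonymously in a mixed paper-pencil and/or QR code mode".
- Abstract: "Subsequent to the EUS-FNB, all enrolled patients will complete the Beck Anxiety Inventory (BAI", again together with the modified DASS-21.

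Other sections show which period matters to the trial. The Introduction gives the aim as evaluating "the efficacy of colorful graphic novels in reducing anxiety in adult patients waiting for an endoscopic-guided biopsy for pancreatic lesions". Under Study design, "the graphic novel will be provided to the patients after the initial colloquium, leaving them waiting for the procedure with the graphic novel". The Discussion says of anxiety before endoscopy or biopsy that "this discomfort typically manifests in the waiting room".

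Statistical analysis summarises BAI and mASS-14 scores, compares the groups, and correlates the two scales. It mentions no baseline score, change score or repeated measurement.

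**The concern.** In this trial the time of measurement largely determines what is being measured. The intervention acts between the colloquium and the procedure, and the anxiety named in the aim belongs to the same interval. A questionnaire completed just before transfer describes that state directly. One completed after EUS-FNB describes it only through recall, with the experience of the procedure and relief at its being over mixed in.

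Two things are at stake. If the after wording is followed, a real effect on waiting anxiety could be diluted. If some staff follow one sentence and some the other, one column of scores holds two different states. The analysis as described could not separate them unless the time of completion had been recorded.

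**Working it through.** The article states no sample size, effect size or standard deviation, so there is no figure to reproduce. The check is a comparison of texts, followed by a bound on the consequence.

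**Step 1: do the sentences concern the same forms?** Yes. The second sentence of Assessing anxiety refers back to the questionnaires just named, and the only ones named are the BAI and the mDASS-21.

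**Step 2: count the timing statements.**

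| Place | Time given |
|---|---|
| Abstract | after EUS-FNB |
| Assessing anxiety, first sentence | after EUS-FNB |
| Assessing anxiety, second sentence | before EUS-FNB |

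Two say after and one says before.

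**Step 3: could both be meant?** Two administrations would remove the literal conflict. However, no section states two, and Statistical analysis describes nothing that would use a second score. Figure 1 might show the schedule, but it could not be consulted. Even if it were clear, the sentences would still need to agree with it.

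**Step 4: compare with the aim.** The comic is read during the wait (Study design). The aim is anxiety during the wait (Introduction), and the Discussion places the discomfort in the waiting room. The before statement fits this chain. The two after statements put the measurement outside it.

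**Step 5: bound the dilution.** Three symbols are needed, none of which the article supplies:

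- d is the true difference between arms in waiting anxiety.
- f is the share of forms completed after the procedure, assumed equal in both arms.
- r is the fraction of d that a post-procedure form still reflects, assumed to lie between 0 and 1.

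The expected observed difference is

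d × [(1 − f) + f × r] = d × [1 − f × (1 − r)].

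| f | r | Observed difference |
|---|---|---|
| 0 | any | d × [1 − 0] = d |
| 0.5 | 1 | d × [1 − 0.5 × 0] = d |
| 0.5 | 0 | d × [1 − 0.5 × 1] = 0.5 d |
| 1 | 1 | d × [1 − 1 × 0] = d |
| 1 | 0 | d × [1 − 1 × 1] = 0 |

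The range runs from no dilution to complete dilution. These rows are illustrations under assumed values, not estimates. The article gives no basis for choosing f or r.

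**The case against.** The strongest reply has four parts.

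- **The schedule may be clear elsewhere.** Figure 1 could show one time point or two, and a full protocol could describe a before-and-after design. This limits what can be said about the intended schedule. It does not remove the conflict between adjacent sentences, and nothing in the article's analysis supports a two-time-point design.

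- **A form given afterwards can still look back.** A reader might infer that post-procedure questionnaires measure only relief and recovery, and no longer the anxiety of waiting. The document does not support that. The mDASS-21 response anchors in Assessing anxiety are worded in the past tense, and the top one refers to most of the time, so they could cover the wait. The forms themselves (Figures 3 and 4) were not available to show the recall period. This objection stands, and it is why the point is put as may not capture. Recall mixed with the procedure experience is nevertheless a different measurement from a score taken during the wait, and the text gives no instruction to recall the wait.

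- **The aim is wider than the wait.** The Abstract and Study design speak more generally of stress and behavioural reactions in patients due for EUS-FNB. A post-procedure score is therefore not plainly out of scope. It remains a weaker fit to the one sentence that states the aim, in the Introduction.

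- **Further consequences are not documented.** A reader might also infer that patients have been sedated or have heard an early impression of the result by then, or that those with a cancelled or aborted procedure would lose their outcome. The article describes neither sedation nor disclosure of results, gives no cancellation rate, and does not say that such patients could not complete a form. Nor does listing a preoperative anxiety scale under Data collection fix when the BAI and mDASS-21 are given. None of this is relied on here.

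**Conclusion.** The contradiction is plain on the face of the text and needs correcting. The same two questionnaires are placed before and after the procedure in consecutive sentences, and the Abstract repeats the placement that fits the stated aim less well. Because the planned group comparison rests on these scores, the ambiguity affects the trial's main result, and a score taken at the wrong time cannot be recovered by analysis.

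The size of the effect on the result cannot be computed. It runs from none to complete dilution, depending on the residual effect in post-procedure forms and on the share completed afterwards. That range assumes the same share in both arms and a residual effect between none and full. It would be wrong to state as fact that the effect would be halved or lost, since that takes the residual effect to be zero.

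**What to change.** Reconcile the Abstract and Assessing anxiety to one primary time point for the BAI and mDASS-21, and amend Figure 1 if it differs. For the stated aim, that point is after the colloquium and the reading period and before transfer to the endoscopy room, at the same stage in both arms. Saying only that the forms precede the procedure would not be enough, because a form filled in before the comic has been read could not show its effect.

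If a post-procedure questionnaire is wanted, define it as a separately labelled secondary outcome and keep its scores apart from the primary ones. Recording the time of completion would allow adherence to be checked.

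The cost is protocol wording, a staff instruction and slight coordination with the endoscopy list. No extra patients are needed.

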### Statistical analysis

The analysis will be performed using jamovi software (the jamovi project, version 2.3, 2023) with R language (R Core Team, 2022). Descriptive statistics will be used to analyze the patients’ socio-demographic and physical characteristics. BAI and mASS-14 scores will be summarized through mean value, standard deviation (SD), maximum, median, and interquartile range (IQR) as necessary. Comparisons between groups will be performed according to the most appropriate statistics (Fisher or χ-squared for categorical variables, parametric or non-parametric statistics for comparisons of continuous variables). Any relation between BAI and mASS-14 scores will be measured through a linear correlation coefficient.

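### The stated mASS-14 subscale range (0–14) and severity bands contradict the item scoring: seven items scored 0–3 give 0–21, so scores 15–21 have no class

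*Protocol article*

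**What the plan says.** All the elements stand in one paragraph of the protocol article, under Assessing anxiety.

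- Source scale: the DASS-21 "originally consisted of 21 items divided into three subscales (anxiety, stress, and depression) with seven items each".
- Modification: "We focused on the anxiety and stress subscales, so we modified the questionnaire by removing the depression subscale". No item is said to be taken out of the two retained subscales, and no rescaling is described.
- Item scoring: "Each item is rated on a 4-point scale from 0 (did not apply to me at all) to 3".
- Stated range: "The total score for each subscale ranges from 0 to 14 in our modified version".
- Severity classes, given once for both anxiety and stress: "normal (0–4), mild (5–8), moderate (9–11), or severe (12–14").

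The Statistical analysis section then uses the instrument: "BAI and mASS-14 scores will be summarized through mean value, standard deviation (SD), maximum, median, and interquartile range (IQR) as necessary". It adds between-group comparisons, chosen by type of variable, and a linear correlation between the two scores.

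**The concern.** A stated score range should follow from the number of items and the item scoring. Here it does not, and the severity bands are built on the same wrong maximum.

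The mASS-14 is one of only two scores named in the Statistical analysis section. As written, patients with the highest anxiety or stress scores cannot be placed in any class. A correctly computed maximum above 14, which the plan intends to report, would also appear to be a data error. The same paragraph says that the modified version will itself be evaluated, which makes its range and classes part of what the study has to get right.

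**Working it through.** **Inputs** (all from Assessing anxiety): 7 items per subscale; 2 subscales kept; item scores 0 to 3; stated maximum per subscale 14; bands 0–4, 5–8, 9–11 and 12–14.

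**1. Can the stated maximum be reproduced?** The maximum of a summed subscale is the number of items times the maximum item score.

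- As described: 7 × 3 = 21, not 14.
- Both subscales summed: 14 × 3 = 42.
- Subscale score doubled: 2 × 21 = 42.
- Some other number of 0–3 items: 3k = 14 has no whole-number solution.
- Seven items scored 0–2: 7 × 2 = 14, but this contradicts the 0–3 item scale.
- Fourteen items scored 0–1: 14 × 1 = 14, but this contradicts both the item scale and seven items per subscale.

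No reading that keeps the stated item scoring gives 14. The number does equal the items kept, 2 × 7 = 14, which is a plausible origin of the slip.

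**2. Coverage of the bands.** A 0–21 score has 22 possible values. The bands cover 0 to 14, which is 15 values. The remaining 22 − 15 = 7 values (15 to 21) have no class: 7/22 = 32% of possible values. A patient answering 2 to every item scores 7 × 2 = 14, the top of severe. A patient answering 3 to every item scores 21 and is unclassified.

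**3. Position of the bands.** Each band is shown as a share of the maximum (limit ÷ 14 and limit ÷ 21):

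| Class | Score | Share of 14 | Share of 21 |
|---|---|---|---|
| Normal | 0–4 | 0–29% | 0–19% |
| Mild | 5–8 | 36–57% | 24–38% |
| Moderate | 9–11 | 64–79% | 43–52% |
| Severe | 12–14 | 86–100% | 57–67% |

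On the real range every band sits lower than the stated range suggests. A raw sum therefore falls into a higher class than a reader who takes 0–14 as the full range would expect.

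**The case against.** The best defence is that the planned analysis survives. The Statistical analysis section summarises the scores, compares them between groups and correlates them with the BAI. If the items are simply added as rated, all of this works on 0–21 whatever the prose says, and both arms are scored alike. No comparison by severity class is named; the general mention of Fisher or chi-squared tests for categorical variables could cover one but does not specify it. The study is a pilot, the BAI is untouched, and item-level responses would allow rescoring. All of this stands, and it limits the consequences.

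It does not remove the contradiction. The questionnaire figure is not shown, but it could not reconcile the text, because no number of 0–3 items gives a maximum of 14. Nor is this a detail that an article leaves to a fuller document: the range and bands are stated, and they conflict with the scoring stated beside them.

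Four stronger readings are tempting, and the documents do not support them:

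- **Truncated scores and a diluted difference between arms.** A reader might infer that the electronic form caps entries at 14. The Data collection section gives no field limits, and its list of scales names the DASS-21 rather than the modified version, so this is conjecture.
- **A large share of patients unclassified.** The 32% counts possible values, not patients. The documents give no score distribution. Under an assumed beta-binomial model for the 0–21 score (precision 6), the share above 14 runs from 0.7% at a mean item score of 0.5 to about 50% at 2.0. The assumption decides the answer.
- **Most scores misclassified through rescaling.** Multiplying the raw sum by 2/3 to fit 0–14 would change the result for many scores, but the protocol describes no such rescaling, and any count that includes 15–21 repeats the gap already reported.
- **Separate bands needed for anxiety and stress.** This may be so, but it depends on source cut-offs that the documents do not give. Misclassification against those cut-offs cannot be measured here either.

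**Conclusion.** The point holds as an internal contradiction that needs no outside source. The subscale range is 0–21, not 0–14, and the total over 14 items is 0–42. Seven of the 22 possible subscale scores have no severity class, and the severe band covers 57–67% of the true maximum rather than its top 14%.

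The conclusion assumes only what the text says: seven items in each retained subscale, scored 0 to 3 and summed without rescaling. What is wrong is the severity classification and the reported range. Comparisons of raw summed scores between arms are unaffected provided that items are summed as rated. How many patients would be unclassified cannot be determined from the documents.

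**What to change.** Before any scoring:

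1. State the range as 0–21 for each subscale and 0–42 for the 14 items together.
2. Make sure that data entry accepts subscale scores up to 21.
3. Reconcile the severity bands with the item scoring so that they cover 0–21, and state how they were derived; otherwise drop them.
4. Say that between-arm comparisons use the continuous subscale scores.

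The cost is a change of protocol wording and a check of the data-entry limits. No extra data are needed. The timing matters: choosing a metric or bands after the scores have been seen would be a post hoc decision.
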